### **Handling protocol deviations or losses to follow-up**

All randomized on-study EPT infants will be assessed for study endpoints even if there are major protocol deviations or they are deemed ineligible. For the primary outcome, any infant that dies at <7 days will be considered an intervention failure. For any surviving infant who has not had a HUS day 7-10 this will be a protocol deviation and there will be a reminder and an

extension to day 14. If a surviving infant has no HUS from day 7-14 this will be a protocol violation and the next available HUS after day 14 will be used for determination of the primary outcome. For secondary outcomes it is highly unlikely that data will be unavailable in the medical records of the delivery hospital until discharge home or 36 weeks PMA (whichever comes first). For infants who are transferred, study coordinators will contact the transfer hospital for secondary outcomes to 36 weeks PMA, with maternal consent. In the rare instances where there is insufficient information, secondary outcomes will be assessed based upon the latest information after consensus review by PIs or the DSMC, as described in the MOP.

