Of note, infants randomized to the “Standard” group will be getting 30-60 seconds of DCC, which is within the range of previous clinical trials and is the current recommendation from ACOG. It is not known whether 120 sec of DCC is more beneficial than 30-60 sec. This would not be feasible to study for this population, since most practitioners would not accept delaying resuscitation of non-breathing EPT infants for 120 seconds during DCC.

The study intervention cannot be blinded but the primary outcome will be assigned by expert radiologists at non-study institutions who will be blinded to study arm.

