**PI: [name] Version**

**Date: August 29, 2023**

- IVH (most severe grade during hospitalization)
- Cerebellar hemorrhage
- Cystic periventricular leukomalacia (cPVL)
- Patent Ductus Arteriosus (PDA) requiring pharmacological or surgical treatment
- Early-onset septicemia (<72h from birth) (positive blood culture and at least 5 days of antibiotic therapy)
- Spontaneous intestinal perforation (SIP) requiring surgery or peritoneal drain
- Necrotizing enterocolitis (Modified Bell's stage 2-3)
- Bronchopulmonary dysplasia (receiving continuous supplemental oxygen at 36 weeks PMA)
- Severe ROP (stage 3 or treated with laser or bevacizumab) prior to 36 weeks PMA

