## **8 ADVERSE EVENTS AND REPORTING**

Extremely preterm infants commonly have multiple clinical complications and laboratory abnormalities associated with prematurity, and those listed in section 6 will be collected and analyzed as secondary outcomes. These outcomes will be collected in the MuSIC database at times indicated in the MOP and reviewed monthly by the UVA Study Team. The DSMC will receive regular reports of secondary outcomes and compare rates in infants in the two study arms and compare overall rates in study infants to reported rates for EPT infants at NICUs in the Vermont Oxford Network or similar databases. If there is a significant imbalance of secondary outcome rates between the study arms or compared to current EPT rates, the proper course of action will be discussed by the study PIs and the DSMC.

Adverse events deemed related (definitely, probably or possibly) to a mother or infant being in the study will be collected and reported, as defined below. Recording of such adverse events will start at the time of the study intervention (birth) and will stop at the time of hospital discharge after delivery for mothers and at discharge home or 36 weeks PMA for infants. Any adverse events not resolved at the time a subject goes off study will be recorded as 'ongoing'.

Adverse events must be assessed for expectedness, severity, attribution (relatedness to the study intervention), and seriousness by the site Investigator, or another qualified study team member.

Adverse events deemed related to the intervention must be reported as SAEs if they become serious.

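### Secondary outcomes with insufficient data may be settled by the PIs or the DSMC, and the protocol does not require that review to be masked to arm

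*Protocol*

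**What the plan says.** The rule is in section 7 of the protocol, Handling protocol deviations or losses to follow-up. It has three steps.

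- Missing data are expected to be uncommon: "For secondary outcomes it is highly unlikely that data will be unavailable in the medical records of the delivery hospital" up to discharge home or 36 weeks.
- Real data are sought first: "For infants who are transferred, study coordinators will contact the transfer hospital for secondary outcomes to 36 weeks PMA, with maternal consent".
- The fallback is introduced by "In the rare instances where there is insufficient information". In those cases "secondary outcomes will be assessed based upon the latest information after consensus review by PIs or the DSMC", with the procedure left to the MOP.

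On knowledge of the arm, section 1 (Rationale for Study Design) says "The study intervention cannot be blinded". The masking that the protocol describes covers the independent radiologists' head-ultrasound readings (sections 1 and 6). Section 8 says "The DSMC will receive regular reports of secondary outcomes and compare rates in infants in the two study arms". The Safety paragraph of section 6 has both the study team and the DSMC looking for differences between arms. Under Guidelines for Safety Monitoring in section 7, the PIs follow high-grade IVH monthly, with monitoring bounds kept separately for each arm.

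**The concern.** This is not a detail left open for an analysis plan. The protocol names who decides, names the basis for the decision, and has a value assigned rather than recorded as missing. The two groups it names may have seen the emerging comparison, and nothing in the text withholds the infant's arm from them.

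Two things are at stake. First, a judgement made with the arm known can misclassify outcomes differently in the two arms. Unlike ordinary missing data, that error is invisible afterwards, because the assigned value looks like an observed one. Second, the DSMC's role is blurred. A committee that monitors secondary outcomes by arm should not also decide what some of those outcomes are.

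**Working it through.** **1. Who decides, and what they can know.**

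| Group named in the rule | What the protocol says about its access |
|---|---|
| PIs | Intervention is open (section 1); monthly follow-up of high-grade IVH, with bounds per arm (section 7); they discuss outcome imbalances between arms with the DSMC (section 8) |
| DSMC | Compares secondary outcomes between arms (section 8); reviews diagnoses for differences between arms (section 6, Safety) |

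Neither row shows that a reviewer of one infant's record is told the arm. Together they show that knowledge of the arm is possible and that no stated step prevents it.

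**2. Which outcomes the rule can reach.** Section 6 lists six neonatal secondary outcomes.

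- Four are complete by day 10: 5-minute Apgar, lowest hematocrit, blood-pressure medication and number of transfusions. Loss after transfer hardly touches them.
- Composite severe brain injury uses the early or the late head ultrasound. The late scan is defined as the birth-hospital scan closest to 36 weeks, so relying on the last birth-hospital scan is the definition for every infant and is not created by this rule.
- Death before 36 weeks, as yes/no, is exposed. An infant last known alive before 36 weeks needs a judgement to be given a value.

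Bronchopulmonary dysplasia, which is defined by oxygen use at 36 weeks, is listed as tertiary in section 6. Section 8, however, says that the complications listed in section 6 are analysed as secondary outcomes. On that broader use of the word, the rule also reaches 36-week outcomes such as this one.

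**3. Size.** The protocol states no missing or transfer rate, so there is no figure to reproduce and what follows is an illustration.

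Inputs:
- N = 940 in total; 172 per arm in cohort 1 and 298 per arm in cohort 2 (section 7, Study Size Considerations).
- Event rate p = 9.6%, the Vermont Oxford Network mean for high-grade IVH (section 7). It stands in for an unspecified secondary event, because the protocol gives no rate for death.
- Assumed: share affected m, equal in both arms; between-arm gap f in the rate assigned to those infants; no true effect.

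Formulas:
- Number affected = m × 940. At 1%, 9.4; at 2%, 18.8; at 5%, 47.
- Standard arm rate = (1 − m)p + m[p + f(1 − p)]. VentFirst arm rate = (1 − m)p + m·p(1 − f). The difference is m × f.
- False-positive rate: two-sided 5% test of two proportions, normal approximation, unstratified.

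Example with m = 5%, f = 0.5 and 172 per arm. The rates are 0.0912 + 0.05 × 0.548 = 0.1186 and 0.0912 + 0.05 × 0.048 = 0.0936. The difference is 2.5 points and the false-positive rate is 11.7%.

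| Share affected | Gap f | Spurious difference | False positives, 172 per arm | False positives, 298 per arm |
|---|---|---|---|---|
| 1% | 0.25 | 0.25 points | 5.1% | 5.1% |
| 1% | 0.5 | 0.5 points | 5.3% | 5.5% |
| 1% | 1 (extreme) | 1 point | 6.1% | 6.9% |
| 2% | 0.25 | 0.5 points | 5.3% | 5.5% |
| 2% | 0.5 | 1 point | 6.1% | 6.9% |
| 2% | 1 (extreme) | 2 points | 9.3% | 12.6% |
| 5% | 0.25 | 1.25 points | 6.7% | 8.0% |
| 5% | 0.5 | 2.5 points | 11.7% | 16.8% |
| 5% | 1 (extreme) | 5 points | 30.4% | 47.8% |

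At about 1% the effect is slight. At 5% it could matter, but only if the assigned rates differ widely by arm.

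**The case against.** The case for leaving the text alone is substantial, and most of it stands.

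- The sentence defers procedure to the MOP, which is not shown and may already withhold the arm. This stands for masking. It does not remove the DSMC from a role that the protocol itself gives it.
- The rule is a last resort, used after the receiving hospital has been asked, and in cases called rare. This stands and limits the size.
- The primary outcome has its own rule and masked central reading. This stands; the primary outcome is unaffected.
- For survival, section 7 (Analyses of the Secondary and Tertiary Endpoints) plans Kaplan-Meier estimation and a stratified log-rank test, so an infant lost while alive can be censored. This stands for that analysis. Section 6 also lists death before 36 weeks as yes/no, and there a value would still have to be assigned.
- A gap of 50 points or more in assigned rates means nearly systematic bias, for which there is no evidence. This stands; the table is a range of what could happen.

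A reader might also infer more than the text supports:

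- That lost infants receive their last value carried forward. The rule describes a case-by-case judgement on the most recent evidence. It does not prescribe carry-forward.
- That the rule understates cystic periventricular leukomalacia. The late scan is by definition the birth-hospital scan closest to 36 weeks, so the rule adds nothing there.
- That bronchopulmonary dysplasia is necessarily overstated. That presumes both the broad use of the word secondary and a mechanical reading of oxygen status at transfer, and neither is fixed by the text.

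**Conclusion.** The point holds in a limited form. The protocol lets the PIs or the DSMC settle secondary outcomes by agreement when data are insufficient, and it states no masking of that review in an open trial where both can see outcomes by arm. This permits arm-aware assignment without showing that it occurs, and it has the DSMC setting values it also monitors. The exposure is mainly death before 36 weeks as yes/no and, if secondary is used as broadly as in section 8, other 36-week outcomes.

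The size rests on assumed shares and gaps. With 1% affected and a 50-point gap, the spurious difference is 0.5 points and the false-positive rate is 5.3% to 5.5%. With 5% and the same gap, it is 2.5 points and 11.7% to 16.8%. If cases are as rare as the protocol expects, the effect is small. This is a cheap improvement and does not threaten the trial's main conclusion.

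**What to change.** Replace the last sentence of Handling protocol deviations or losses to follow-up with wording to this effect:

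*If information on a secondary outcome is still insufficient after the transfer hospital has been contacted, any judgement is made by study clinicians from a record from which the arm and the delivery-room data have been removed. The DSMC takes no part. An outcome that cannot be established is recorded as missing; for survival, the infant is censored at last contact.*

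The sentence should also say whether it covers the outcomes that section 6 calls tertiary, since section 8 uses secondary more broadly. The censoring clause agrees with the Kaplan-Meier analysis already planned in section 7. If the MOP already requires a masked review, its procedure needs only to be brought into line.

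The cost is one amended sentence, redaction of a few records, and a few more missing values. No new committee is needed.

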### **Participant Enrollment and Follow-Up**

As noted in Section 7.2, we anticipate being able to obtain consent, randomize, and perform the study intervention for about 40% of the estimated 2500 EPT births at all study centers over the 5 year period of the study, which will allow us to reach the targeted enrollment of 940 EPT infants.

## **8 ADVERSE EVENTS AND REPORTING**

Extremely preterm infants commonly have multiple clinical complications and laboratory abnormalities associated with prematurity, and those listed in section 6 will be collected and analyzed as secondary outcomes. These outcomes will be collected in the MuSIC database at times indicated in the MOP and reviewed monthly by the UVA Study Team. The DSMC will receive regular reports of secondary outcomes and compare rates in infants in the two study arms and compare overall rates in study infants to reported rates for EPT infants at NICUs in the Vermont Oxford Network or similar databases. If there is a significant imbalance of secondary outcome rates between the study arms or compared to current EPT rates, the proper course of action will be discussed by the study PIs and the DSMC.

Adverse events deemed related (definitely, probably or possibly) to a mother or infant being in the study will be collected and reported, as defined below. Recording of such adverse events will start at the time of the study intervention (birth) and will stop at the time of hospital discharge after delivery for mothers and at discharge home or 36 weeks PMA for infants. Any adverse events not resolved at the time a subject goes off study will be recorded as 'ongoing'.

Adverse events must be assessed for expectedness, severity, attribution (relatedness to the study intervention), and seriousness by the site Investigator, or another qualified study team member.

Adverse events deemed related to the intervention must be reported as SAEs if they become serious.

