**Criteria for evaluation:**

**Efficacy:** Head ultrasound imaging 7-10 days after birth and other clinical outcomes

**Safety:** Incidence and severity of Serious Unanticipated Events, SAEs and AEs determined to be related or possibly related to the intervention.

**Statistical methods:** The study is designed as a Phase III, two-arm, randomized, multicenter comparative study of **Standard** versus **VentFirst** cord clamping in extremely preterm infants in two cohorts of infants (those **breathing well** and those **not breathing well**). Analyses will be performed separately within each cohort.

**Efficacy:** The primary analysis will be based on all randomized eligible EPT infants, and will be based on the arm they were randomized to regardless of intervention received (intent-to-treat). The primary outcome of the trial is based upon the central review of the head ultrasound and is the proportion of EPT infants who are alive without any grade IVH on head ultrasound obtained 7-10 days following birth. The primary outcome classification is binary and the stratified Cochran-Mantel-Haenszel test for relative risk will be used for the final comparison of intervention arms.

**Safety:** All randomized EPT infants will be evaluable for adverse events from the time of delivery. Adverse events will be tabulated by frequency and severity, overall and by arm as well as by cohort. Differences in the level of adverse events by study intervention will be assessed by classifying them as severe or not severe and examining the relative proportion of severe events.

LIST OF ABBREVIATIONS

| Abbreviation or specialist term | Explanation                                            |
|----------------------------------------|---------------------------------------------------------------|
| AE                                     | Adverse Event                                                 |
| ACOG                                   | American College of Obstetrics and Gynecology                 |
| AAP                                    | American Academy of Pediatrics                                |
| BPD                                    | Bronchopulmonary Dysplasia                                    |
| CBC/Diff                               | Complete Blood Count and differential                         |
| CPAP                                   | Continuous Positive Airway Pressure                           |

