## **Safety**

Safety will be monitored in all randomized/on-study mothers and infants by comparing primary and secondary outcomes and reportable adverse and serious adverse events between study arms, as described in sections 8 and 9. This includes but is not limited to outcomes reported to be different in preterm infants undergoing delayed versus immediate cord clamping such as hematocrit in the first 24h after birth, bilirubin in the first 10d after birth, indicators of adverse cardiovascular transition in the delivery room and first 24h after birth, intraventricular hemorrhage, and other complications of extreme prematurity. The UVA Study Team and DSMC will regularly review these events and diagnoses for differences between study arms and differences from standard rates for EPT infants in international databases such as Vermont Oxford Network.

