### **Definitions**

#### **Adverse Event**

Generally, an adverse event is any untoward medical occurrence in a subject who has received an investigational intervention.

Specific to this study, as noted above, common complications of prematurity will be collected and analyzed as secondary outcomes.

Adverse events judged to be related to being in the VentFirst study will be considered for AE reporting, as below.

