### Attribution Assessment (Relatedness)

The site principal investigator, or qualified designee, will evaluate all AEs and assess their relatedness, if any, to the study intervention. The following criteria will be used to define relatedness:

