### Reportable Serious Adverse Events

Generally, a serious adverse event is one that is temporally associated with the subject's participation in a research study that results in death or disability, is life-threatening, or prolongs hospitalization. Many of the typical complications of prematurity fit this description and only the following SAEs possibly related to the study will be reported as such.

| Serious Adverse Event                                                                                     | Timing                                                               |
|-----------------------------------------------------------------------------------------------------------|----------------------------------------------------------------------|
| Mother                                                                                             |                                                                      |
| Any condition leading to death                                                                            | Prior to discharge                                                   |
| Post-partum hemorrhage $\geq$ 1000 mL                                                                     | In the first 24h after delivery (including delivery room blood loss) |
| Serious unexpected adverse event judged to be definitely or probably related to being in the study | Any time                                                             |
| Infant                                                                                             |                                                                      |
| Any condition leading to death                                                                            | Prior to 36 wks PMA                                                  |
| Chest compressions or epinephrine in DR                                                                   | In the delivery room                                                 |
| IVH grade 3-4                                                                                             | On 7-10 day HUS or 36 week PMA HUS                                   |
| Cerebellar hemorrhage                                                                                     | On 7-10 day HUS or 36 week PMA HUS                                   |

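### The protocol does not settle whether a listed adverse event judged unrelated is still reported, so open-label attribution could enter the between-arm AE comparisons

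*Protocol*

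**What the plan says.** Three places make relatedness the way in for adverse event data.

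- Section 8, opening text: "Adverse events deemed related (definitely, probably or possibly) to a mother or infant being in the study will be collected and reported".
- Section 8, Adverse Event definition: "Adverse events judged to be related to being in the VentFirst study will be considered for AE reporting, as below".
- Synopsis, Criteria for evaluation: the safety criterion covers "SAEs and AEs determined to be related or possibly related to the intervention".

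A fourth place, Reportable Serious Adverse Events, can be read the same way: "only the following SAEs possibly related to the study will be reported as such".

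The assessment is local: "The site principal investigator, or qualified designee, will evaluate all AEs and assess their relatedness, if any, to the study intervention". The protocol states that the intervention cannot be blinded, and only the central head-ultrasound reading is described as blinded to arm.

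Other text reads as unconditional. Section 4 (Mother, OB team) has large post-partum hemorrhage noted as an SAE, and retained placenta and delivery-related infection reported as AEs, with no relatedness test. The Reportable Adverse Events table is a fixed list of events that require reporting. Section 9 requires expedited reporting of any SAE in the SAE table.

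The data are then compared by arm. Section 6 (Safety) plans monitoring by "comparing primary and secondary outcomes and reportable adverse and serious adverse events between study arms". The synopsis and Section 7 (Analyses of the Secondary and Tertiary Endpoints) compare AEs by intervention, classed as severe or not severe.

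**The concern.** A site investigator who knows the arm decides whether an event counts as related. The Standard arm is current practice, so a complication of prematurity there is easily put down to another cause. The same complication after ventilation on an intact cord is harder to dismiss. If that judgement decides whether the event is recorded, the numerator of the AE rate depends partly on knowledge of the arm. Placing all randomized mothers and infants in the safety population fixes the denominator but not the numerator.

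The effect could run either way. Readier attribution in VentFirst would create an apparent excess. Investigators who favour VentFirst and attribute less could hide a real one. Because sites can read the text differently, the filter may also vary between sites.

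**Working it through.** **Step 1. The rules side by side.**

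| Place in protocol | Event judged related | Listed event judged not related |
|---|---|---|
| Synopsis, safety criterion | counted | not counted |
| Section 8, opening text and AE definition | collected | not collected, if read literally |
| SAE table introduction | reported | unclear: the relatedness phrase may describe the list or filter each case |
| Section 4, maternal events | reported | reported |
| AE table (fixed rows) | reported | reads as reported |
| Section 9, SAEs in the table | expedited | reads as expedited |

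No sentence resolves the third column. Within the tables, only the rows for other AEs and for serious unexpected events carry an explicit case-by-case condition.

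**Step 2. What escapes the filter.** Section 8 says the complications in Section 6 are collected and analysed as outcomes, and that the DSMC compares outcome rates between arms. Matching the AE and SAE tables against Section 6:

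- Maternal hemorrhage, infection and retained placenta have counterparts.
- So do admission hypothermia, pneumothorax, low-blood-pressure medication, compressions or epinephrine, hematocrit, bilirubin, IVH, cerebellar hemorrhage, cystic leukomalacia, NEC and infant death.
- Maternal death and exchange transfusion have none.

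High-grade IVH is also monitored by arm and cohort without attribution (Section 7, Guidelines for Safety Monitoring).

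**Step 3. What remains exposed.**

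1. Unlisted events, which enter only by attribution.
2. The severity comparison. The grading scale applies to AEs, while Section 6 items are mostly yes/no or measured values.
3. Maternal death and exchange transfusion.
4. Any listed event in the AE and SAE records at a site that applies the opening condition to it.

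**Step 4. How large it could be.** The protocol gives no attribution rates, so there is no figure to reproduce. Everything below is assumed, except 940 infants with equal allocation, which gives 940 / 2 = 470 per arm.

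Recorded rate = true rate × probability of being judged related.

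Chance of p < 0.05 (two-sided) = Φ((|r1 − r2| − 1.96·SE0) / SE1), with SE0 from the pooled rate and SE1 from the separate rates.

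True rate 10% in both arms, 50% of VentFirst events attributed, so r1 = 0.10 × 0.50 = 0.05:

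- 40% of Standard-arm events attributed: r2 = 0.04, SE0 = 0.01352, SE1 = 0.01352, so Φ((0.010 − 0.02651) / 0.01352) = 11%.
- 25% attributed: r2 = 0.025, SE0 = 0.01239, SE1 = 0.01237, so Φ((0.025 − 0.02429) / 0.01237) = 52%.

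| Standard-arm attribution | Recorded RR | True rate 5% | 10% | 20% |
|---|---|---|---|---|
| 50% (equal) | 1.0 | 5% | 5% | 5% |
| 40% | 1.25 | 7% | 11% | 19% |
| 25% | 2.0 | 29% | 52% | 83% |
| 10% | 5.0 | 71% | 95% | >99% |

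A filter that works equally in both arms leaves the relative risk unbiased but costs information. For a true 15% versus 10%, power is 64% with all events recorded. It is 20% when a quarter are recorded in each arm (3.75% versus 2.5%).

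**Step 5. A limit on this arithmetic.** It applies to rates per infant. If the severity comparison uses the severe share of reported events, that share is s·a / (s·a + (1 − s)·b), where s is the true severe share and a and b are the attribution probabilities for severe and other events. With a = b it equals s. Distortion then needs a/b to differ between arms.

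**The case against.** The strongest reply is that relatedness is set mainly for the list and not case by case. The Expectedness paragraph says the protocol includes events linked to delayed clamping in earlier studies, and then asks investigators to add other events they think may be related. The opening sentence of Section 8 defers to definitions further on. A relatedness condition in the residual rows would be redundant if every row were already filtered. Read this way, the present design already reports listed events for everyone. This is a fair reading and probably the intended one. It does not remove the conflict, because the synopsis, the opening text and the AE definition say otherwise and nothing tells a site which governs.

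Three stronger readings are tempting and are not supported.

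- *Adverse events are collected only if judged related.* This is wrong for most safety data, given the unfiltered Section 6 outcomes. The plausible harms (hypothermia, pneumothorax, hypotension treatment, compressions, maternal hemorrhage) are all among them.
- *The Standard arm receives no study intervention, so its events cannot qualify.* The Section 7 design table lists Standard as one of two interventions, and the opening sentence refers to being in the study, which covers both arms. What does stand is that the attribution paragraph uses the study intervention as its test, which is more readily met in VentFirst.
- *The between-arm safety comparison is distorted.* No attribution data are given, so this is a risk and not a demonstrated bias.

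**Conclusion.** The conflict is real and worth correcting, but its reach is limited. Two sets of passages give different answers on whether a listed event judged unrelated is reported, and the filtered version depends on open-label local judgement. The comparisons at risk are the AE severity comparison (synopsis and Section 7) and the reportable AE/SAE part of the safety comparison in Section 6. The outcome-based comparison seen by the DSMC is not affected.

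Size and direction cannot be taken from the protocol. With modest assumed differences in attribution (50% versus 40%) the false-positive chance rises from 5% to between 7% and 19% over true rates of 5% to 20%. Only large differences make it severe. These figures assume 470 infants per arm and a per-infant analysis of events that pass through the filter. The SAP was not available. It could define the analysis, but it could not recover events that sites never recorded.

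**What to change.** 1. In the synopsis safety criterion, the opening of Section 8, the AE definition and the SAE table introduction, state that every event named in the AE and SAE tables is recorded and reported for all randomized mothers and infants in both arms, whatever its attribution. This brings them into line with Section 4, the AE table and Section 9.
2. Keep the relatedness judgement as a descriptor of each event, and as the entry condition for unlisted events only.
3. In the synopsis, Section 6 (Safety) and Section 7, base the between-arm AE and SAE comparisons on listed events, with all randomized mothers or infants as the denominator. Report unlisted, attribution-filtered events descriptively.

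The cost is protocol wording, a notice to sites and somewhat more AE entries. Most listed events are already abstracted from the routine record for Section 6. If sites have already worked under the present wording, the occurrence of most listed events can be checked against the Section 6 data. Maternal death, exchange transfusion and severity grades would need a separate look.
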